## Abstract

**Background:**

HIV incidence among pregnant and postpartum women remains high in South Africa. Pre-exposure prophylaxis (PrEP) use remains suboptimal in this population, particularly during the postpartum period when women’s engagement with routine clinic visits outside PrEP decreases. Key barriers to sustained PrEP use include the need for ongoing contact with the health facility and suboptimal counseling around effective PrEP use.

**Methods:**

Stepped Care to Optimize PrEP Effectiveness in Pregnant and Postpartum women (SCOPE-PP), is a two-stepped unblinded, individually randomized controlled trial (RCT) that aims to optimize peripartum and postpartum PrEP use by providing a stepped package of evidence-based interventions. We will enroll 650 pregnant women (> 25 weeks pregnant) who access PrEP at a busy antenatal clinic in Cape Town at the time of recruitment and follow them for 15 months. We will enroll and individually randomize pregnant women > 16 years who are not living with HIV who are either on PrEP or interested in starting PrEP during pregnancy. In step 1, we will evaluate the impact of enhanced adherence counselling and biofeedback (using urine tenofovir tests for biofeedback) and rapid PrEP collection (to reduce time required) on PrEP use in early peripartum compared to standard of care (SOC) (*n* = 325 per arm). The primary outcome is PrEP persistence per urine tenofovir levels and dried blood spots of tenofovir diphosphate (TFV-DP) after 6-months. The second step will enroll and individually randomize participants from Step 1 who discontinue taking PrEP or have poor persistence in Step 1 but want to continue PrEP. Step 2 will test the impact of enhanced counseling and biofeedback plus rapid PrEP collection compared to community PrEP delivery with HIV self-testing on PrEP use (n = up to 325 postpartum women). The primary outcome is PrEP continuation and persistence 6-months following second randomization (~ 9-months postpartum). Finally, we will estimate the cost effectiveness of SCOPE-PP vs. SOC per primary outcomes and disability-adjusted life-years (DALYs) averted in both Step 1 and 2 using micro-costing with trial- and model-based economic evaluation.

**Discussion:**

This study will provide novel insights into optimal strategies for delivering PrEP to peripartum and postpartum women in this high-incidence setting.

**Trial registration:**

NCT05322629: Date of registration: April 12, 2022.

## Background

Women in sub-Saharan Africa face high HIV acquisition risk during pregnancy and breastfeeding with HIV incidence doubling during pregnancy and the postpartum period compared with non-pregnant/breastfeeding women [1–3]. Seroconversion during pregnancy or breastfeeding substantially increases the risk of vertical transmission, and accounts for nearly one-third of all infant HIV infections [4, 5]. As fertility rates in the region remain high [6], high HIV risk during pregnancy and postpartum translates to a substantial cumulative period of risk for women spanning over decades of women’s lives, underscoring the urgent need for prevention interventions tailored to at-risk pregnant and postpartum women. While the elimination of mother-to-child transmission (eMTCT) services have expanded rapidly in the region [7–9], few prevention interventions exist for most pregnant women who initially test HIV-negative. This is a major missed opportunity that has implications for women, their partners, and infants.

The World Health Organization (WHO) recommends offering pre-exposure prophylaxis (PrEP) to pregnant and postpartum women at risk for HIV acquisition as a female-controlled prevention strategy [10–12]. The South African National PrEP guidelines were updated in 2020 to include offering PrEP to PBFW not living with HIV [13]. However, current oral PrEP (TDF-FDC) must be taken daily for it to be effective. PrEP persistence in women has been low in South Africa and surrounding countries [14–18]. Our PrEP in pregnant and postpartum (PrEP-PP) study was one of the first studies to integrate PrEP into government maternal and child health care services in South Africa. Preliminary findings from the study show high levels of PrEP initiation (> 85% of eligible women), but low levels of continuation on PrEP (< 60% of women at 6 months postpartum) [19]. Innovative PrEP optimization strategies are needed to reach PBFW at risk of HIV acquisition, particularly postpartum.

Barriers to optimal PrEP use among PBFW span across health facility-, intrapersonal-, and interpersonal-levels. In surveys and in-depth interviews with women on PrEP, our team found that many women underestimated their partner’s risk of living with HIV [20–22]. Women often reported needing permission from their partners to use PrEP and feared disclosing to their partners that they are taking PrEP. Noticeable drop-offs in clinic visits for PrEP collection and PrEP persistence among postpartum women were largely contributed to decreased clinic attendance postpartum (as women no longer attended antenatal care (ANC) services) and periods of postpartum abstinence where they had low risk of HIV acquisition and therefore stopped taking PrEP [23–25]. For postpartum women, PrEP consultations may be the only reason to visit the facility, adding substantial time and travel burden. Finally, standard PrEP counseling is based on self-reported persistence, which may over report drug persistence and therefore miss opportunities for in-depth, tailored persistence counseling that meet individual clients’ needs [26].

Stepped care to optimize PrEP effectiveness in pregnant and postpartum women (SCOPE-PP) is a two stepd, unblinded, individually randomized controlled trial (RCT) that aims to optimize postpartum PrEP use by providing a stepped package of evidence-based interventions. The intervention includes two steps implimented across two steps of the RCT: Step 1 intervention arm includes the offer of enhanced adherence counselling through biofeedback of tenofovir levels following a rapid urine tests and rapid PrEP collection (following HIV self-testing, [HIVST]); Step 2 women with poor PrEP continuation or persistence in Step 1 to either, (a) rapid PrEP (following HIVST) and the choice of commuinty PrEP pick-up points, or (b) biofeedback adherence counseling in the clinic. Intervention arms will be compared to the standard of care PrEP delivery per the South African National Department of Health guidelines [27]. As part of the study we will estimate the cost effectiveness of SCOPE-PP vs. SOC per primary outcomes and disability-adjusted life-years (DALYs) averted in both Step 1 and 2 using micro-costing with trial- and model-based economic evaluation. By identifying optimal strategies for delivering PrEP to PBFW, this study can improve upon exisiting PrEP strategies to decrease HIV acquisition and vertical transmission in the region.

## Methods

### Aims

The aims of the study are to:*Aim 1*: Evaluate the impact of SCOPE-PP interventions on PrEP persistence in pregnancy and early postpartum (peripartum) (Step 1) and postpartum women (Step 2)Step 1 (randomize 650 pregnant women actively taking PrEP at the time of enrollment):Intervention: Enhanced adherence counseling through biofeedback and rapid PrEP collection following HIVSTPrimary Outcome 1: PrEP continuation and persistence per urine tenofovir (TFV) at 6-months after randomization (verified post hoc via dried blood spots [DBS] analysis of tenofovir diphosphate [TFV-DP]).Hypothesis 1: Enhanced adherence counseling and rapid PrEP collection will improve PrEP continuation and persistence by > 15%.Step 2: We will randomize ~ 325 postpartum women from Step 1 who disengaged from PrEP during the first 6-months post enrollment and desire to stay on PrEP to:Intervention 1: Rapid PrEP collection following HIVST and differentiated model of community-based PrEP delivery.Intervention 2: Enhanced adherence counseling through biofeedback in the clinic and rapid PrEP collection following HIVSTPrimary Outcome 1: PrEP continuation and persistence per urine TFV at 6-months after randomization in Step 2 (verified post hoc via DBS analysis of TFV-DP).Hypothesis 2: Among postpartum women who struggle to engage with PrEP within the first 6-months postpartum, differentiated PrEP delivery (in community pick up points) will improve PrEP continuation and persistence by > 15% compared to standard-of-care (intensive counseling and facility PrEP delivery) at 12-months postpartum.*Aim 2****:*** Evaluate the cost effectiveness and equity impact of SCOPE-PP vs. standard of care. Within a trial-based cost-effectiveness analysis, we will estimate provider costs and primary outcomes of SCOPE-PP in terms of PrEP continuation and persistence per urine tenofovir at 6-months and 6-months after randomization in Step 2. Thereafter, in a model-based economic evaluation that integrates HIV-infections averted, we will estimate HIV-treatment cost offsets in order to estimate lifetime costs and DALYs averted. The resulting incremental cost per DALY averted will be compared to a South African cost-effectiveness threshold to assess value for money [28].

### Trial design

We will conduct a two-stepped (i.e., two randomization points), unblinded individually randomized controlled trial (RCT) that aims to optimize postpartum PrEP use by providing a stepped package of evidence-based interventions. The RCT takes a pragmatic approach and utilizes routine providers for intervention delivery to promote fidelity for real-world settings.

### Setting

This study will be implemented in the Gugulethu Midwife Obstetrics Unit (MOU) in Cape Town. Gugulethu’s population of 300,000 is predominantly of low socioeconomic status (SES). This township has 48% unemployment rate and 64% of the adult population live on ~$35 USD per month. The population uses public-sector health services that are provided free at the point-of-use. In 2018, the HIV prevalence among women attending ANC services provided by the MOU was 27% with > 80% of women breastfeeding. We will build on the existing infrastructure at each clinic and train routine providers on the PrEP intervention to be provided within clinical visits. Additional study visits will be provided in a research site behind the clinic by trained UCT qualitative and quantitative interviewers who speak the local language, isiXhosa.

### Conceptual framework

We adapted Ickovics’ and Meisler’s conceptual framework with factors affecting persistence in HIV treatment [29] to place our study and its outcomes into a broader persistence context (Fig. 1). The conceptual factors are categorized by 1) facility-level, individual-level, 2) and 3) HIV-level from the participants’ perspective which were key factors for pregnant and postpartum persistence in our PrEP-PP study [22, 23].

**Fig. 1 Fig1:**
[figure not shown]
Conceptual framework for SCOPE-PP study

### Ethical review

The study protocol, informed consent form, all data collection tools, and other requested documents have been reviewed and approved by the University of Cape Town Faculty of Health Sciences Human Research Ethics Committee (UCT-HREC). University of California Los Angeles IRB has provided ethical reliance on UCT-HREC. Participants will be reimbursed for their time and transportation (15USD/R120/per study visit) to the clinic for each study visits (no reimbursement for travel undergone to collect PrEP in the clinic or community in Step 2).

#### Step 1: EARLY-PREP IN PERIPARTUM

##### Recruitment and enrolment

Pregnant women who are on PrEP or initiate PrEP at baseline visit will be recruited and screened for eligibility during their routine ANC services at gestational > 25 weeks using a set script for screening and a brief description of the study. We have recruited over 1300 pregnant women in our prior study in 18 months and are confident that we can continue to recruit from this facility. We will obtain written informed consent immediately following screening.

The inclusion criteria for Step 1 include:Age ≥ 16 years (16- and 17-year-old pregnant adolescent girls will provide unassisted consent)> 25 weeks pregnantPlans to deliver at the study facility (or nearby hospital)Documented HIV-negative (per national protocol for routine ANC),Lives within 20 km of the study facilityOn PrEP prior to study or interested in starting PrEP in study visitWilling and able to consent to study participation.

Individuals not meeting the above criteria will be excluded and referred to SOC PrEP services.

##### Randomization (Fig. 2)

For Step 1 (pregnant women on PrEP or wanting to start PrEP at the time of enrollment), individual women will be randomized using a 1:1 ratio to either:Standard of Care (SOC) orEnhanced adherence counselling through biofeedback and rapid PrEP collection.

**Fig. 2 Fig2:**
[figure not shown]
SCOPE-PP Study Design: Step 1 and Step 2

After enrolling in the trial and completing a baseline survey, PBFW will be assigned immediately to a study ID based on the randomization list. Study ID’s will be linked with the pre-assigned blocked randomization by the study data manager and pre-loaded into the tablet device but will be unknown to the study staff until survey and randomization modules are completed and saved, ensuring randomization cannot be manipulated by the study staff. Once finalized, the randomization results will appear on the tablet device as a picture on a pre-programmed tablet, and will be shown to the participant to maximize transparency and study buy-in.

##### Standard of care

Women randomized to the SOC arm (*n* = 325) will receive facility-based PrEP, blood-based, provider administered HIV testing and PrEP counseling monthly during pregnancy and quarterly during postpartum. Women will also receive HIV self-screening kits (HIVST) during each facility visit to take home to their sexual partners, per South African HIV testing guidelines. PrEP prescriptions and HIV testing will be provided according to the national PrEP guidelines in 3 monthly intervals [13].

##### Intervention (step 1; Table 1)

Women randomized to the intervention arm (*n* = 325) will receive SOC services (described above) plus bio-feedback persistence counseling based on urine lateral flow assays of TFV to measure recently daily adherence including rapid PrEP delivery following HIVST. Intervention steps are detailed below.**Real-time novel immunoassay using urine that measures TFV and enhanced bio-feedback counseling (10 minutes):** This immunoassay (UrSure, OraSure Technologies, Inc.) is sensitive (100%) and specific (97%) when compared to plasma TFV levels [30] and will be used to identify women who may need additional counseling or differentiated PrEP delivery. The novel urine assay shows TFV concentrations if TDF is taken in the past 48 hours thereby enabling counselors to provide feedback on persistence levels, immediately at point of care. Prior studies, including our own pilot in postpartum women [21] have demonstrated the efficacy, feasibility, and acceptability of urine TFV testing.**Enhanced counseling (15 minutes):** includes:Feedback of urine TFV test results to encourage continued persistence or the development of a plan for how improve daily use, especially prior to and during periods of sexual activity (prevention effective adherence)Counseling on the importance of knowing the partners’ serostatus (and possibility of serodiscordant results), andAll other SOC counseling topics, including highlighting the risk of seroconversion and the importance of PrEP persistence and regular quarterly HIV testing while on PrEP.**Rapid PrEP collection (3 minutes):** At study enrollment clients will be given HIV self-test kits (HIVST) to be used for themselves, in addition to their partners if they do not know their serostatus. Prior to the repeat PrEP clinical visit (every 3 months), participants can personally use a HIVST kit and share a photograph of results or actual used HIVST kit to speed up the PrEP collection process. Those with a non-reactive HIVST kit will forego additional HIV testing at that visit (cutting at least 15 minutes from PrEP collection procedures). Women can collect a pre-packaged 3-month supply of PrEP following adherence counseling and monitoring of side effects.

**Table 1 Tab1:** Study and clinic visits by intervention and standard of care arms in Step 1 of RCT in SCOPE-PP study, Cape Town, South Africa

RCT Step 1: EARLY PrEP-P	SOC (***n*** = 325)	Intervention (***n*** = 325)	Steps and measurement
**Randomization of pregnant women on PrEP (= > 25 weeks gestation)**			
**Baseline Study visit**	In clinic: PrEP offer, standard counseling	In clinic: PrEP offer, standard counseling	In study site (behind clinic): • Consent form • Survey • Reimbursement for time
**1 month clinic visit**	In clinic: PrEP refill and standard counseling, urine testing (no feedback)	In clinic: PrEP refill with urine testing and feedback on PrEP levels in urine	Standard monitoring No reimbursement for time
**3 month Study visit**	In clinic: PrEP refill and standard counseling, urine testing (no feedback) With standard HIV testing/HIVST	In clinic: PrEP refill with urine testing and feedback on PrEP levels in urine With standard HIV testing/HIVST	In study site: • Blood collection • Survey • Reimbursement for time
**6 month** **Study visit**	In clinic: PrEP refill and standard counseling, urine testing (no feedback) With standard HIV testing/HIVST	In clinic: PrEP refill with urine testing and feedback on PrEP levels in urine With standard HIV testing/HIVST	In study site: • Blood collection • Survey • Reimbursement for time
**If participant continues on PrEP and adherent based on urine testing, can continue in study according to following visits. If not adherent or discontinues, can participate in RCT Step 2 (LATE-PREP-P).**			
**9 month clinic visit**	In clinic: PrEP refill and standard counseling, urine testing (no feedback) With standard HIV testing/HIVST	In clinic: PrEP refill with urine testing and feedback on PrEP levels in urine With standard HIV testing/HIVST	Standard monitoring No reimbursement for time
**12 month Clinic visit**	In clinic: PrEP refill and standard counseling, urine testing (no feedback) With standard HIV testing/HIVST	In clinic: PrEP refill with urine testing and feedback on PrEP levels in urine With standard HIV testing/HIVST	Standard monitoring No reimbursement for time
**15 month Study visit**	In clinic: PrEP refill and standard counseling, urine testing (no feedback) With standard HIV testing/HIVST	In clinic: PrEP refill with urine testing and feedback on PrEP levels in urine With standard HIV testing/HIVST	In study site: • Blood collection • Survey • Reimbursement for time
**End of study and referral for ongoing PrEP care in clinic**			

##### In case of a seroconversion

In both arms, women on PrEP with a reactive result will be followed up by study staff and counseled to stop taking PrEP immediately until they confirm their serostatus and initiate ART. If they are unable to attend the facility, study staff will do a home visit to follow up.

### Data collection

#### Baseline survey

Participants will complete a baseline survey immediately following enrollment. The baseline survey will collect key data on socio-demographic information, partner and pregnancy history, HIV risk (including sexual activity, partner HIV status and risk perception), prior use of PrEP and attitudes about PrEP, and information on IPV and substance use. All surveys will be conducted in the local language by trained study staff using electronic tablets with REDCap software. Participants who report substance use, violence and/or IPV will be referred to a local NGO for social services and counseling in addition to study activities.

#### Follow-up surveys

Participants will complete 4 follow-up surveys every 3 months (study follow-up visits separate from clinical PrEP visits). Follow-up surveys will document any changes in HIV risk, sexual activity, and PrEP persistence, including pill count. Self-reported adverse events, side effects and any occurrence of IPV or alcohol use will also be documented.

#### Study retention

We will ask participants to share their phone numbers as well as the contact of someone clost to them. Study staff will call and SMS participants in both study arms to participate in their study visits. We will conduct home visits if they miss > 1 visit.

#### Concomitant care

all antental and postnatal care is permited during the trial. Participation in other HIV trials is prohibited.

#### Outcomes

The primary outcome for Step 1 is early PrEP continuation and persistence per urine TFV at 6 months postpartum (verified post hoc via DBS analysis of TFV-DP - high persistence is defined as having levels above 2 pills per day or = > 650 fmol/punch in pregnant women and = > 950 fmol/punch in postpartum women) [31]. Secondary outcomes include:**Perfect PrEP persistence:** we will measure perfect PrEP persistence (e.g., level of objective PrEP persistence measured with DBS of TFV-DP through peripartum and postpartum period at 6 and 12 months following PrEP start) as well as “prevention-effective” [32, 33] adherence among participants, which measures PrEP use prior to (7+ days) and during times of sexual activity (using self-reported recent sexual activity). We will use benchmarked blood levels from IMPAACT 2009 results for pregnant and postpartum women as= > 650 fmol/punch in pregnant women and = > 950 fmol/punch in postpartum women [31].**HIV incidence** in participants (measured at each follow-up survey using SOC HIV tests)**Uptake of male partner HIV testing**, measured as the proportion of male partners who test (either through HIVST or standard facility-based testing), as reported by the female participantNumber of participants reporting adverse events (i.e., side effects, IPV, end of relationship)

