#### Step 2 (Table 2)

Differentiated PrEP distribution strategies are needed to optimize PrEP, especially in postpartum women who struggle to stay engaged in care. Similar to community-based ART delivery, we will test a differentiated PrEP delivery model for options for community PrEP delivery and pick up for postpartum women who want to continue on PrEP, but either discontinue, or have poor persistence in Step 1.

**Table 2 Tab2:** Study and clinic visits by intervention and standard of care arms in Step 2 of RCT in SCOPE-PP study, Cape Town, South Africa

*If PrEP discontinued, missed visit, or poor persistence (no TFV in urine) offer new randomization (RCT 2) with chance of differentiated PrEP delivery*			
	Counseling group	Community delivery group	Steps
**Baseline study visit**	In clinic: PrEP refill and counseling with urine testing and feedback	At community pick up points^a^: PrEP refill + HIV self testing for monitoring HIV status	In study site (behind clinic): • Consent to new randomization • Survey • Reimbursement
**3 month Service visit**	In clinic: PrEP refill and counseling with urine testing and feedback	At community pick up points^a^: PrEP refill + HIV self testing for monitoring HIV status	Standard monitoring • No reimbursement for time
**6 month Service visit**	In clinic: PrEP refill and counseling with urine testing and feedback	In community^a^: PrEP refill + HIV self testing for monitoring HIV status	Standard monitoring No reimbursement for time
**9 month Study visit**	In clinic: PrEP refill and counseling with urine testing and feedback	In community^a^: PrEP refill + HIV self testing for monitoring HIV status Referral to continue on PrEP at local clinic	In study site: • Blood collection • Survey • Reimbursement for time

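### HIV incidence is defined by standard-of-care tests at follow-up surveys, but the only HIV test scheduled in Step 1 is a clinic test that a self-test can waive in the intervention arm alone

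*Protocol article*

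**What the plan says.** **Outcome definition.** The Step 1 Outcomes section lists HIV incidence as a secondary outcome "in participants (measured at each follow-up survey using SOC HIV tests". The Step 2 Outcomes section carries it over.

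**SOC arm, Step 1.** The Standard of care section gives these women "blood-based, provider administered HIV testing and PrEP counseling monthly during pregnancy and quarterly during postpartum". It also gives them self-test kits, but for their partners. The same section later puts HIV testing at 3-monthly intervals, so it states two frequencies.

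**Intervention arm, Step 1.** Before each 3-monthly PrEP visit, "participants can personally use a HIVST kit and share a photograph of results or actual used HIVST kit". Then: "Those with a non-reactive HIVST kit will forego additional HIV testing at that visit".

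**Schedules.** Table 1 shows a standard test/HIVST entry in the clinic columns of both arms from month 3. Its study-site column lists blood collection, a survey and reimbursement at months 3, 6 and 15, and no HIV test. In Table 2 the community arm has "PrEP refill + HIV self testing for monitoring HIV status"; the study-site column lists blood collection at month 9 only, again with no HIV test.

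**Data source.** Table 4 takes HIV incidence from RedCap clinical data, monthly.

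**The concern.** The definition promises the same test in every woman at every survey. The schedule and Table 4 point instead to the test done during routine PrEP care, and that is where the two Step 1 arms part. One arm is tested by a provider. The other may be tested by the woman herself before she arrives, with the result shown by photograph.

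The trial is unblinded. If the self-test route picks up fewer infections, or picks them up later, the intervention arm will show lower HIV incidence without any protective effect. The error runs in one direction, towards the arm under test, and intention-to-treat analysis does not remove it.

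**Working it through.** The protocol gives no event count, power or test sensitivity for HIV incidence, so there is no figure to reproduce. The check is a comparison of sections, followed by an illustration on stated assumptions.

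**1. Where is the outcome test scheduled?**

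| Source | Test | Setting |
|---|---|---|
| Outcomes (Step 1) | SOC HIV test, all women | Follow-up survey |
| Table 1, clinic columns | Standard test/HIVST, both arms, from month 3 | Clinic |
| Table 1, study-site column | None listed (blood and survey at months 3, 6, 15) | Study site |
| Table 2, study-site column | None listed (blood and survey at month 9) | Study site |
| Table 4 | Clinical data, monthly | Not stated |

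The follow-up survey sections state four surveys, one every 3 months, in each step. Table 1 shows follow-up surveys at three visits and Table 2 at one. The survey visits that would carry the outcome test are therefore not fully scheduled either.

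**2. Does the scheduled test differ by arm?**

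- Step 1: yes. Only the intervention section contains the waiver, and SOC women receive kits for partners.
- Step 2: not shown. The Step 2 Intervention section has rapid collection following HIVST in both arms. Table 2 names a test only for the community arm.

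**3. What size could the Step 1 effect have?**

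Input from the protocol: 325 women per Step 1 arm, with the primary assessment at 6 months. Assumptions, none given in the protocol: equal true incidence of 1 to 4 per 100 person-years; self-test uptake *u* of 25% to 100%; sensitivity *r* of the self-test route relative to the SOC test of 0.70 to 1.00.

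Expected true cases per arm = 325 × 0.5 years × incidence:
- 325 × 0.5 × 0.01 = 1.6
- 325 × 0.5 × 0.04 = 6.5

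Observed rate ratio (intervention/SOC) under no effect = *u* × *r* + (1 − *u*):

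| *r* | *u* = 25% | *u* = 50% | *u* = 100% |
|---|---|---|---|
| 1.00 | 1.00 | 1.00 | 1.00 |
| 0.90 | 0.975 | 0.95 | 0.90 |
| 0.70 | 0.925 | 0.85 | 0.70 |

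Cases missed at a test, full uptake = cases × (1 − *r*): from 1.625 × 0.05 = 0.1 (at *r* = 0.95) to 6.5 × 0.30 = 2.0 (at *r* = 0.70).

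**The case against.** The best defence is that the definition already supplies the common test. The Follow-up surveys section says study visits are separate from clinical PrEP visits, the waiver covers only the PrEP visit, and blood is drawn at the study site in both arms. An SOC test at each survey is then possible, and a reader who infers that the protocol explicitly replaces the outcome test with a self-test goes too far. The defence does not close the gap, because no schedule lists that test and Table 4 names clinical data. Surveys are also held in REDCap, so the Table 4 entry alone is not decisive, but monthly timing matches no survey schedule.

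The Table 1 entry for the SOC arm can also be read as a provider test plus kits for partners, so it need not contradict the Standard of care section.

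Other stronger readings are tempting but unsupported:

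- *A woman can hide a reactive self-test by not sharing it.* Only a non-reactive result that is shown earns the waiver; a woman who shares nothing gets none. What remains is that the test is done before the visit and may be shown only as a photograph.
- *The Step 2 arms are tested differently.* Both collect PrEP after HIVST, and a counsellor is available at the community site.
- *Infections present at enrolment bias the comparison.* Step 1 entry requires "Documented HIV-negative (per national protocol for routine ANC") without a date, and Table 1 lists no test before month 3. Randomization balances such infections in expectation, so they affect the rate more than the contrast.
- *Large losses accumulate over 15 months.* About half of the women are expected to be re-randomized around month 6. Infection also persists and testing repeats, so one missed test is often a delayed detection and not a lost case.
- *The DALY results are distorted.* The model integrates infections averted, but nothing says that trial seroconversions feed it; Table 4 gives its data source as not applicable.

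**Conclusion.** The concern holds for Step 1 in this form: the outcome definition and the testing schedule are not reconciled, and followed as scheduled they give ascertainment that depends on arm. Any shortfall in self-test detection would favour the intervention.

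The size cannot be found from the protocol. The illustrated null rate ratio of 0.70 to 1.00 rests wholly on assumed relative sensitivity at full uptake. It moves closer to 1 as uptake falls, and there is no bias if the two tests are equally sensitive. With only about 1.6 to 6.5 expected cases per arm over 6 months, the absolute error is at most about two cases at a test on these assumptions, although that is a large share of so few events.

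For Step 2 the defect is narrower: self-testing is not the SOC test that the definition names. Because HIV incidence is a secondary outcome for which no power is claimed, this should be corrected but is not a must-fix.

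**What to change.** For outcome ascertainment, perform the same SOC blood HIV test in every woman in every arm at the study visits where blood is already collected (Step 1 months 3, 6 and 15; Step 2 month 9), whatever any self-test showed. List it in the study-site columns of Tables 1 and 2. Base the arm comparison of HIV incidence on it, and still count confirmed seroconversions found at other visits, so that cases in women who later miss a study visit are not discarded.

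Leave the self-test route for PrEP refills as it is; it is part of the intervention. Reconcile the Standard of care section, the Step 1 Intervention section, Tables 1, 2 and 4 and the Outcomes definition, so that they agree on which test, at which visit, defines a case.

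Cost: changes to wording and tables, one added test on blood already drawn, and a few minutes at the study site, outside the rapid collection process under test.
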